### Secondary objectives and endpoints

Secondary objectives are improvement of vigilance/awareness measured via alternative scales using the following: Richmond Agitation-Sedation Scale (RASS), Full Outline of UnResponsiveness (FOUR) Score Coma Scale, Glasgow Outcome Scale – Extended (GOS-E) and Coma Recovery Scale revised (CRSR). Further secondary outcome variables include functional outcome using National Institute of Health Stroke Scale (NIHSS) regarding potential stroke severity and modified ranking score (mRS) in follow-up after discontinuation of medication and after three months. The incidence of complications regarding delirium will be assessed using the Intensive Care Delirium Screening Checklist (ICDSC). The Montreal Cognitive Assessment (MoCA) will assess the neuropsychological outcome. Regarding validity of these measures for determining outcome, please see the paragraph below.

Any adverse event (AE) (any untoward medical occurrence including an abnormal laboratory finding, regardless of its causal relation to the study treatment) will be recorded during the whole study period.

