### Clinical assessment scales

#### Consciousness

Different rating scales will quantify the clinical severity of disorders of consciousness.

The GCS rates patients based on their ability to perform limb and eye movements as well as to speak. These three categories represent the core elements of the scale: „eye“, „verbal“, and „motor“. A person’s GCS score can range from 3 (completely unresponsive) to 15 (completely responsive). This score is fast, easily and reliably to perform and can be used in emergency situations and also to monitor hospitalized patients. Regarding the assessment of amantadine treatment effects, it has already been used in the context of traumatic brain injury [28] as well as within a retrospective analysis of Leclerc et al. (2021) in post-stroke patients [29].

The FOUR Score is a 17-point scale with possible scores ranging from 0 to 16 (decreasing score is associated with a worsening level of consciousness). The FOUR score overcomes some of the shortcomings of the GCS by assessing the four domains of neurological function: eye responses, motor responses, brainstem reflexes, and even breathing pattern [30].

The RASS is a ten-step scale for assessment and quantification of sedation as well as agitation with the value ‘0’ describing the physiological state [31].

The GOS-E is a scale for patients with brain injuries, such as cerebral traumas or strokes that groups the victims by the objective degree of recovery [32]. Later, the same authors proposed to split the 3 better categories (severe disability to good recovery, i.e., 3 to 5) in lower and upper sub-categories, leading to the extended version of the scale (GOS-E) which includes 6 plus 2 (death and vegetative state), i.e., 8 categories in total [33].

The CRS-R is a standardized neurobehavioral assessment instrument for the usage in patients with disorders of consciousness. It is intended to establish diagnosis, monitor recovery, predict outcome as well as assess treatment effectiveness [34].

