#### Statistical analysis

The study is successful if a total of 13 of 43 patients show success (improvement of at least 3 points on the GCS). Using the two-stage optimum design of Simon for Phase II trials, non-evaluable patients have to be replaced. However, if the necessary number of 13 successes is achieved with less than 43 patients, there will be no early stopping for success. Calculations have been done with a Simon design calculator presented by the NIH on the internet: http://linus.nci.nih.gov/cgi-bin/simonr/cgi_main.

The primary endpoint *improvement of the GCS score from screening up to day 5 of at least 3 points* is analyzed according to the Simon design as described above. The primary analysis population is the per protocol population. This population includes all patients with GCS measurement at day 6 and all patients who died until day 6 (failures). No planned subgroup analyses will be performed. The secondary endpoints (mRS, NIHSS, GOS-E, CRS-R, MoCA after 90 days, RASS and ICDSC) will be analyzed by mixed models with time (categorially coded) as only factor including all measurements up to 3 months follow up. In case of severe violation of normal distribution assumption data will be analyzed by nonparametric tests (Friedmann with including pairwise comparisons using Nemenyis test). No imputation of missing values is planned. P-values will be computed, significances are only “local” in the sense that they are not corrected for multiple testing. The only confirmatory analysis is the one for the primary endpoint.

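### One time-only rule for all secondary scales leaves later deaths unscored on most of them, reads raw RASS as if higher were always better, and gives MoCA no usable baseline

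*Protocol article*

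**What the plan says.** The Statistical analysis section names the scales, "The secondary endpoints (mRS, NIHSS, GOS-E, CRS-R, MoCA after 90 days, RASS and ICDSC", and fixes one method for all of them: they "will be analyzed by mixed models with time (categorially coded) as only factor including all measurements up to 3 months follow up". If normality is severely violated, the fallback is "nonparametric tests (Friedmann with including pairwise comparisons using Nemenyis test". It adds: "No imputation of missing values is planned". Deaths until day 6 count as failures for the primary endpoint. The article states no rule for later deaths or for deaths on the secondary scales.

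The scale descriptions matter here. GOS-E has "6 plus 2 (death and vegetative state), i.e., 8 categories in total". RASS is a "ten-step scale for assessment and quantification of sedation as well as agitation", with 0 as the physiological state, and the secondary objectives use it as a measure of improved vigilance. On delirium and cognition the objectives say: "The incidence of complications regarding delirium will be assessed using the Intensive Care Delirium Screening Checklist (ICDSC"), and "The Montreal Cognitive Assessment (MoCA) will assess the neuropsychological outcome".

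Table 2 schedules CRS-R, RASS, ICDSC and GOS-E at Visits 1 to 8, mRS and NIHSS at Visits 1, 7 and 8, and MoCA at Visits 1 and 8. Table 1 requires coma with GCS below 8. The eligibility text also excludes unresponsive wakefulness and the minimally conscious state.

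**The concern.** One rule is applied to scales that behave differently.

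- **Deaths.** The Background calls disorders of consciousness a strong predictor of mortality, so deaths before month 3 are to be expected. On a scale without a death value, a patient who dies has no later scores. The mixed model keeps that patient's earlier rows and treats the later scores as missing at random. The Friedman test needs complete blocks and drops the patient.
- **RASS.** The normal value lies inside the scale. A shift past 0 into agitation moves a mean or a rank in the same direction as recovery.
- **MoCA.** The only scheduled value before Visit 8 falls when every patient is in coma.
- **ICDSC.** The objective is an incidence, but the stated analysis is a score over time.

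The Discussion intends to use these scales to find the best endpoint and to inform outcome choice for a placebo-controlled trial. With one arm there is no control group against which a spurious time trend would cancel.

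**Working it through.** The plan gives no figure for the secondary rule. Its nearby figure, the Simon design (stop below 4 of 13, success at 13 of 43), reproduces: exact alpha 0.0496 at 20% and power 0.8002 at 40%. Nothing below affects it.

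**1. Survivor selection.** The documents give neither 90-day mortality m nor its link to the scores, so both are assumed. Let the true mean change be zero with SD 1, let the change correlate at 0.6 with a latent survival variable, and let the lowest fraction m on that variable die. The survivors' mean change is then 0.6 × φ(z)/(1 − m), with z the m-quantile of the standard normal.

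- m = 20%: 0.6 × 0.280/0.80 = 0.21 SD
- m = 30%: 0.6 × 0.348/0.70 = 0.30 SD (about 30 survivors of 43, t about 1.8)
- m = 40%: 0.6 × 0.386/0.60 = 0.39 SD (about 26 survivors, t about 2.2)

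**2. The mixed model itself.** The figures in step 1 are survivors-only means. A simulation of the maximum-likelihood equivalent of the mixed model used 43 patients, two visits, within-patient correlation 0.5, no true change, and death logistic in the day-90 score.

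| Mortality | Log-odds slope per SD | Apparent gain (SD) | Mixed model rejects at nominal 5% | Friedman rejects |
|---|---|---|---|---|
| 20% | 1 to 2 | 0.13 to 0.21 | 13 to 25% | 7 to 9% |
| 40% | 1 to 2 | 0.26 to 0.40 | 28 to 58% | 11 to 18% |
| 60% | 1 to 2 | 0.39 to 0.61 | 39 to 80% | 13 to 23% |
| any of these | 0 | about 0 | about 5% | about 5% |

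The gain column is the mixed-model estimate. Keeping the earlier rows therefore does not remove the bias.

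**3. Friedman attrition.** Assume 5% of values are missing at random at each visit.

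- Eight-visit scales: 0.95^8 = 0.663, and 0.663 × 43 = 28.5 complete patients. With 30% deaths as well, 28.5 × 0.70 = 20.0.
- Three-visit NIHSS and mRS: 0.95^3 = 0.857, and 0.857 × 43 = 36.9, before deaths.

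**4. RASS.** Assume all 43 start at -4, 33 stay there, and positive values mean agitation.

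- 10 move to 0: 10 × 4/43 = +0.93
- 10 move to +4: 10 × 8/43 = +1.86

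The agitated outcome scores twice as well as the normal one.

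**5. MoCA.** Set Table 2 (Visits 1 and 8) beside the entry criterion of coma. If Visit 1 is missing, or only the 90-day value is meant, time has one level and no time effect exists. If Visit 1 is set to the lowest score, any survivor who scores above it counts as improved.

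**6. ICDSC.** Table 1 excludes delirium with ICDSC above 4 (above 5 in aphasic patients), so a threshold is already defined. A time effect on the score does not estimate an incidence.

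**The case against.** The strongest reply is that the section calls the secondary p-values local and the primary analysis the only confirmatory one. No decision rule uses these tests, and scale-level coding often belongs in an SAP that is not shown. The low stakes stand. The coding argument stands only in part, because the article does not leave the method open: it fixes the model, the fallback and the absence of imputation.

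Several stronger readings are tempting and are not supported:

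- *The rule deletes deaths.* Not in the mixed model, which keeps earlier rows. Nor necessarily on GOS-E, where death is an observable category; what remains there is to say that it is carried to later visits. The article does not say how mRS treats death.
- *The analyses will show improvement whatever happens.* This depends on assumed mortality and an assumed link between death and score. With no link there is no bias, and at 30% mortality the illustrated t of 1.8 falls short of two-sided 5% significance.
- *Friedman keeps only two thirds of patients.* The 66% figure applies to eight-visit scales only, and the fallback applies only under severe non-normality.
- *RASS would score a known effect of the trial treatment as benefit.* The article lists hyperexcitability only under Overdosage, and ICDSC is recorded at every visit at which RASS is recorded.
- *MoCA is expressly tested against baseline.* The text names the 90-day value; the comparison is inferred from Table 2 and the inclusion of all measurements.
- *The ICDSC analysis also favours improvement.* Patients selected for low baseline scores would, if anything, tend to drift upwards, towards apparent worsening.

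**Conclusion.** The concern holds in a limited form. Followed as written, the rule gives results on CRS-R, NIHSS, RASS, ICDSC and MoCA that rest on survivors or on an unstated missing-at-random extrapolation for the dead. It also gives a RASS mean without a clear direction of benefit and a MoCA time effect without meaning.

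The size of the survivor bias is illustrative: about 0.3 to 0.4 SD under a correlation of 0.6 and 30 to 40% mortality, and none if death is unrelated to the score. The RASS and MoCA points need no mortality assumption; the RASS figures of +0.93 and +1.86 illustrate a property of the scale. ICDSC is a mismatch between objective and analysis, not a bias towards benefit. The trial's success criterion does not depend on any of this, but the choice of outcomes for the next trial may.

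**What to change.** Replace the single rule with a short statement per scale:

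- **GOS-E and mRS:** score a death in the GOS-E death category, and in the worst mRS category, at every later visit. Analyse Visit 8 with deaths included.
- **CRS-R and NIHSS:** add a rank-based analysis of change with deaths ranked worst, and label the mixed-model results as conditional on survival.
- **RASS:** analyse distance from 0, and report the percentage agitated.
- **MoCA:** report Visit 8 only, with counts of untestable and dead patients and no time test.
- **ICDSC:** report also the proportion above the protocol's threshold, to match the incidence objective.

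The cost is wording only. The protocol requires an amendment for changes to statistical analysis, but no new data are needed. Ranking deaths worst is one defensible choice among several, which is why it is added beside the mixed model for CRS-R and NIHSS. The secondary results may look less favourable.

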#### Interim analyses

After 13 patients, an interim analysis for futility is performed. The study is terminated early if less than 4 successes are observed. If four or more successes are observed, the study continues with 30 additional patients to recruit a total of 43 patients.

### Methods for additional analyses (e.g., subgroup analyses)

No planned subgroup analyses will be performed.

### Methods in analysis to handle protocol non-adherence and any statistical methods to handle missing data

No imputation of missing values is planned. The analysis population for the primary endpoint is defined as patients who show adherence to the study protocol to at least Visit 6 (GCS measurement after 5 days amantadine) and all patients who died until day 6 (failures). Dropouts before Visit 6 (e.g., anesthesia required) will be excluded from trial.

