### Study procedures

The following general procedures will be part of the study visits: patient history and demographics, documentation of clinical data (age, gender, handedness, intensive care unit and hospital length of stay, mortality, discharge disposition) and drug history, physical and neurological examination, blood tests (especially infection markers and electrolytes), electroencephalography (EEG), electrocardiography (ECG) as well as several questionnaires concerning consciousness and functional clinical outcome. For further details regarding the visit schedule, please see Fig. 1; Table 2. The majority of the concomitant measures are non-invasive and performed as part of the clinical routine in vigilance-reduced intensive care patients. Moreover, intensive and intermediate care unit patients are continuously monitored, so that possible adverse effects can be detected and treated immediately.

**Table 2 Tab2:** Synopsis of planned study visits. The whole study duration for each subject will be 3 months incl. screening and follow-up procedures

	Enrolment		Treatment period					Follow-up	
	Screening/Consent	Visit 1 (baseline and first day of treatment)	Visit 2 (after 24 ± 4 h on amantadine)	Visit 3 (after 48 ± 4 h on amantadine)	Visit 4 (after 72 ± 4 h on amantadine)	Visit 5 (after 96 ± 4 h on amantadine)	Visit 6 (after 120 ± 4 h on amantadine)	Visit 7 (14 days after last dose)	Visit 8* (after 3 months ± 7 days from1st dose)
*Timeline (days)*		*1*	*2*	*3*	*4*	*5*	*6*	*-*	*90*
Informed consent	X								
Inclusion /exclusion criteria	X (using a screening sheet)	X (recheck)							
Patient history, demographics		X							
Documentation of clinical data		X							
Documentation of drug history		X							
Physical and Neurological examination		X							
Blood tests (approx. 10 ml)		X							
Start of trial drug		X							
Responsiveness check				X*					
Pregnancy Test (measurement of hCG in serum) in woman of child bearing potential	X								
GCS		X*	X	X*	X	X	X*	X	X
FOUR Score Coma Scale		X	X	X	X	X	X	X	X
RASS		X	X	X	X	X	X	X	X
ICDSC		X	X	X	X	X	X	X	X
EEG		X					X	X	
ECG		X	X	X	X	X	X	X	
mRS		X						X	X
NIHSS		X						X	X
GOS-E		X	X	X	X	X	X	X	X
CRS-R		X	X	X	X	X	X	X	X
MoCA		X							X
Questionnaire for therapists		X	X	X	X	X	X	X	(X)
Documentation of (S)AE		X	X	X	X	X	X	X	

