### Criteria for discontinuing or modifying allocated interventions 

#### Renal function impairment

As the renal clearance of amantadine is significantly lower in adult patients with moderate or severe renal impairment compared with healthy adults and the renal pathway is a major elimination pathway, impairment in renal function can result in significant accumulation in the plasma. In case of renal insufficiency, the dosage will be modified according to the dose adjustment table (see Table 4).

**Table 4 Tab4:** Dose modification in case of renal insufficiency

Glomerular filtration rate (GFR) in ml/min	Dosage modification in mg	Administration interval
80 − 60	no dosage modification	
60 − 50	no dosage modification	
50 − 30	100 mg	1-1-0 No increase in non-responders
30 − 20	100 mg	1-0-0 no increase in non-responders
20 − 10	100 mg	1-0-0 no increase in non-responders
< 10 or hemodialysis	excluded from trial	

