#### Toxicities

If treatment-related toxicities occur during the study, especially epileptic seizure, spasticity, ECG QTc > 480 ms, or any other suspicious ECG changes or cardial events (e.g., arrythmia, myocarditis, heart failure), drug administration will be terminated immediately. This should be reported as an adverse event.

If hallucinations occur, the dosage will be decreased to 50%. If successful, the administration will be continued with the reduced dosage, otherwise, it will be abandoned entirely. This should be reported as an adverse event.

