### Biostatistician

[name].

**Composition of the data monitoring committee, its role and reporting structure**.

The data monitoring committee (DMC) is formed by the ZKS Tuebingen, Center for Clinical Studies. The DMC is independent from the principle investigator and sponsor. An interim-analysis is performed after 13 patients, undergoing amantadine treatment for at least 5 days. The study is terminated early if less than 4 successes are observed.

**Adverse event reporting and harms**.

**Safety assessment**.

Adverse events (AE), severe adverse events (SAE) and suspected unexpected serious adverse reactions (SUSAR) will be detected as exploratory endpoints within the study. A serious adverse event (SAE) means any untoward medical occurrence that at any dose:

results in death.is life-threatening.requires inpatient hospitalization or prolongation of existing hospitalization.results in persistent or significant disability/ incapacity.results in a congenital anomaly / birth defect.is medically significant (e.g., suspected transmission of an infectious agent via medicinal product).

Planned hospitalizations or prolongation of existing hospitalization as a result of the following causes need not to be reported as SAE:

drug application.test procedure required in the protocol.hospitalizations for diagnostic measures only.technical, practical, or social reasons, in absence of an adverse event.surgical intervention or other measures and the conditions leading to these measures are not AEs, if the condition leading to the measure was present prior to inclusion into the trial.stay at rehabilitation clinic.

Medical Dictionary of Regulatory Activities (MedDRA)-Coding will be used. All AE, SAE and SUSAR occurring after entry into the study and until day 14 after amantadine treatment (Visit 7) will be recorded. Within 24 h of occurrence, the adverse event has to be reported to the ZKS Tuebingen. The principle investigator or sponsor will determine relatedness of an event to study drug and decides potential termination of Amantadine treatment. The study will monitor for the following adverse events daily during patient examination: epileptic seizure, spasticity, ECG QTc > 480 ms, arrythmia, heart failure and hallucinations.

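### Patients who drop out before Visit 6 are removed from the trial and not only from the primary analysis, which conflicts with the safety recording rule and leaves their Visit 7 and 8 follow-up unprovided for

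*Protocol article*

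**What the plan says.** The section on protocol non-adherence and missing data defines the primary analysis population as "patients who show adherence to the study protocol to at least Visit 6", plus deaths up to day 6, and then adds: "Dropouts before Visit 6 (e.g., anesthesia required) will be excluded from trial". The Statistical analysis section describes the same population without an adherence condition: "This population includes all patients with GCS measurement at day 6 and all patients who died until day 6 (failures"). It also says that "non-evaluable patients have to be replaced".

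The safety text, under Adverse event reporting and harms, says: "All AE, SAE and SUSAR occurring after entry into the study and until day 14 after amantadine treatment (Visit 7) will be recorded". Table 2 agrees, with adverse event documentation marked at Visits 1 to 7. The section on secondary objectives and endpoints gives a longer window, the whole study period, which is three months per patient.

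Under Toxicities, for listed events such as seizure, QTc above 480 ms or arrhythmia, "drug administration will be terminated immediately", and the event is to be reported as an adverse event.

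Study procedures lists "documentation of clinical data (age, gender, handedness, intensive care unit and hospital length of stay, mortality, discharge disposition") among the general procedures. In Table 2 the row for documenting clinical data carries a single mark, at Visit 1, the first treatment day.

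**The concern.** The sentence on dropouts sits with the definition of an analysis set but removes patients from the trial itself. A site that follows it would stop collecting data on a patient for whom the safety section still requires recording. No section provides for Visit 7 or Visit 8 in such a patient.

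The abstract names the incidence of adverse events as something the study will investigate, and functional outcome at three months is a secondary endpoint. If early leavers are removed and replaced, later adverse events and three-month outcomes would describe mainly the patients who reached Visit 6, together with the deaths up to day 6. Leaving early is unlikely to be unrelated to clinical course, so the loss would be selective.

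The Visit 1 mark for clinical data is a smaller, separate fault: outcome items are scheduled on a day when they have not yet happened.

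**Working it through.** **The plan's own figure.** The design continues with at least 4 successes in 13 and succeeds with at least 13 in 43. The exact probability of success is the sum over x1 = 4 to 13 of P(X1 = x1) × P(X2 ≥ 13 − x1), with X1 ~ Bin(13, p) and X2 ~ Bin(30, p). This gives 0.0496 at p = 0.20 and 0.8002 at p = 0.40, matching the stated 5% and 80%. The 43 is therefore a sound target for evaluable patients, and this point does not dispute it.

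**The two rules applied to one patient.** Take a patient whose last dose is on day 2 and who is treated as a dropout.

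- Safety section: recording runs to day 2 + 14 = day 16. For a full course it would run to day 5 + 14 = day 19.
- Secondary-endpoint section: recording runs to about day 90.
- Dropout sentence: the patient is out of the trial from the exit.

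Read literally, these cannot all be followed. Visits 7 and 8 would still be definable for this patient, since Table 2 times Visit 7 from the last dose and Visit 8 from the first.

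**Is an early stopper a dropout?** The text does not settle it.

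- For: the sentence stands under a heading on non-adherence and follows a population that requires adherence to Visit 6, described there as the measurement after five days of amantadine. The data monitoring text likewise counts the 13 interim patients as having had at least five days of treatment.
- Against: the Statistical analysis section asks only for a day-6 GCS, and the Toxicities section ends the drug, not participation.

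A patient off the drug with a day-6 GCS is thus inside one definition and arguably outside the other.

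**How many patients.** The document gives no dropout rate, so d is an assumption: the share of treated patients who leave before Visit 6 other than by death. If the trial runs to full size with replacement, the number treated is 43 / (1 − d), rounded up.

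| d (assumed) | 43 / (1 − d) | Treated | Outside the 43 |
|---|---|---|---|
| 5% | 45.3 | 46 | 3 |
| 10% | 47.8 | 48 | 5 |
| 20% | 53.8 | 54 | 11 |
| 30% | 61.4 | 62 | 19 |

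These are counts of patients exposed to the rule. They are not counts of adverse events lost.

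**Effect on three-month outcomes.** The secondary endpoints are analysed by mixed models on all measurements up to three months, without imputation. Such a model can use whatever is collected, but the dropout rule would end collection for these patients.

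**Clinical data in Table 2.** Age, gender and handedness are known at Visit 1. Length of stay, mortality and discharge disposition are not. Mortality has other routes: deaths to day 6 count as failures, fatal serious adverse events are recorded to Visit 7, and GOS-E has a death category and is marked up to Visit 8. The article shows no other route for length of stay or discharge disposition.

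**The case against.** The strongest reply is that the sentence is loose wording. It stands under an analysis heading directly after the primary population, and with replacement of non-evaluable patients it may only mean exclusion from the evaluable 43. A site could stop the drug, report the event, record to day 14 after treatment and treat the patient as non-evaluable. That reading is reasonable, but the text says trial and not analysis, and nothing states that these patients continue to Visits 7 and 8. The definition of a safety population can also be left to an analysis plan. That stands, but the complaint here is a stated rule that contradicts another stated rule.

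Several stronger readings are tempting and are not supported:

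- **Mortality is scheduled only at Visit 1.** Only the clinical-data row is; the three other routes above remain.
- **Those removed tolerated the drug worst.** The only example given is a need for anesthesia, toxicity is not said to end participation, and deaths to day 6 are kept.
- **Toxicity stops would disappear from the count.** The triggering event must be reported as an adverse event, with daily monitoring and reporting within 24 hours.
- **The monitoring board would see filtered data.** Events go within 24 hours to the centre that forms the board, which follows safety while the trial is ongoing.
- **Table 4 repeats the exclusion.** Its entry for GFR below 10 or haemodialysis, "excluded from trial", is most simply read as restating the renal eligibility criterion in Table 1.

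**Conclusion.** The point holds as a conflict between stated rules with a plausible, selective loss of data. The dropout sentence reaches beyond the primary analysis, contradicts both statements of the safety window, and leaves Visit 7 and 8 follow-up after exit unprovided for. What may be lost is adverse events after exit and later outcomes, not the event that led to stopping. How much is lost depends on the dropout rate, which the document does not give, and on whether sites count early stoppers as dropouts. The illustrative 3 to 19 patients rest on assumed rates of 5% to 30% and full enrolment. The Visit 1 scheduling of length of stay, mortality and discharge disposition is a definite but smaller error. The two-stage design figures are unaffected. The text should be corrected.

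**What to change.** 1. In the section on non-adherence and missing data, exclude dropouts before Visit 6 from the primary analysis instead of from the trial, and say whether stopping the drug by itself makes a patient a dropout. Bring the two descriptions of the primary population into line.
2. State that every patient who received at least one dose stays in adverse event recording to at least Visit 7 and is assessed at Visits 7 and 8, unless consent for further data collection is withdrawn.
3. Reconcile the safety window in the secondary-endpoint section with the one in the safety section and Table 2.
4. In Table 2, schedule mortality, length of stay and discharge disposition at Visits 7 and 8, leaving the baseline items at Visit 1.

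No dose or stopping rule needs to change. The cost is an amendment, which the protocol says goes to the local ethics committee, and a few extra follow-up assessments for patients who stop early.
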